## Exclusion Criteria

1. Any dementing illness (AD, vascular dementia, normal pressure hydrocephalus, or Parkinson's disease); dementia defined by CDR  $\geq 1$ , MMSE  $< 24$
2. Significant disease of the CNS such as brain tumor, seizure disorder, subdural hematoma, cranial arteritis
3. Alcohol or substance abuse according to DSM-IV criteria within the last 2 years
4. Major depression, schizophrenia, or other major psychiatric disorder defined by DSM-IV criteria
5. Abnormal labs indicating vitamin B12 deficiency, thyroid disease, or UTI (documented bacterial colonization is acceptable)
6. Unstable or significantly symptomatic CVD (e.g. CAD with frequent angina, CHF with dyspnea at rest)
7. Hypertension: defined as uncontrolled BP  $> 150/90$
8. Clinical symptomatic orthostatic hypotension
9. Diabetes mellitus that requires insulin injections
10. History of cortical stroke
11. Cancer within the last 5 years, with the exception of localized prostate cancer (Gleason Grade  $< 3$ ) and non-metastatic skin cancers (melanoma).
12. Illness that requires  $>1$  visit /month to a clinician
13. Contraindications to MRI (i.e., heart pacemaker, metal plates or objects in head, , claustrophobia)
14. Medications:
  - a. CNS active meds that have not been on stable doses for at least 2 months (cimetidine, beta-blockers, and SSRIs)
  - b. Neuroleptics, antiparkinsonian agents, systemic corticosteroids, and narcotic analgesics; in the case where these were used for a self-limited time they must have been discontinued for a period of five half-lives prior to baseline visit
  - c. Over the counter supplements are not by themselves exclusionary, however, subjects are asked not to change the dosing regimen over the course of the trial unless medically indicated; the presence and dose of these agents are recorded
  - d. A baseline screen plasma PUFA  $> 5.5$  weight percent of total fatty acids for EPA+DHA will confirm supplementation of O3PUFA history. If patient indicates regular supplementation with fish oil on phone screen, can wash out for 4 months prior to study visit one.
  - e. Cholinesterase inhibitors (i.e., Aricept)
  - f. Investigational drugs within five half-lives prior to baseline
  - g. Anticoagulation therapy: Vitamin K antagonist: warfarin (Coumadin, jantoven), Factor Xa inhibitors: rivaroxaban (xarelto), fondaparinux (arixtra), dabigatran (pradaxa), apixaban (eliquis); Low molecular weight heparins: dalteparin (fragmin), enoxaparin (lovenox)(Incident use of anticoagulant therapy will exclude further study drug allocation. However, subjects will be asked to complete all follow-up visits.)

**Study Supplement and Dose.** Because neuronal functioning is dependent on DHA  and EPA may have vascular effects , we have elected to use a combination supplement. Since these pufas also exist together in nature, this form of supplementation will be less likely to create an unfavorable imbalance in fatty acid metabolism compared to a single constituent form, especially during long-term use in an older population. The form and daily dose of EPA and DHA was chosen because it is a form used in a previous randomized, double-blind, placebo-controlled study in elders with mild to moderate AD (Table 5). This dose was able to significantly increase both EPA and DHA levels in RBC membranes at 6 and 12 months in study participants randomized to receive fish oil (n=13 at both time points), and was associated with an excellent safety profile (Figure and Table 6). This dose also penetrates the threshold plasma levels associated with neuroprotection in our preliminary and published studies. The study supplement will contain one of the following and all study supplements will be taken with meals: 1) Each ProOmega 3 (Nordic Naturals) soft gel contains 1 gram of fish oil concentrate guaranteed to have a concentration of long-chain omega 3 fatty acid ethyl esters at 70%, primarily EPA (325 mg/g) and DHA (225 mg/g). Three capsules is the daily dose, which will provide a total of 1650 mg of omega 3 pufas (975 mg EPA + 675 mg DHA) per day; 2) Placebo oil contains soybean oil.

**Outcome Measures.** Measures of executive function and processing speed appear sensitive to WMH progression. Our preliminary data found plasma omega 3 pufas associated with WMH volume and age-related decline in domains known to be sensitive to WMH accumulation (Trail B and Digit Symbol). We intend to use the same psychometric measures to determine omega 3 pufa supplementation effects. An axial view of a 3T FLAIR MRI will be utilized at screening to determine total WMH volume and permit entry of subjects with 5 cc or >. MRI derived total WMH volume is a primary outcome measure. The Clinical Dementia Rating scale will confirm non-demented state as CDR < 1.

**Recruitment and Enrollment:** A de-identified scan of the OHSU clinical database identified 6,571 men and women age 80 and older that have visited our medical center within the past year, without a dementing illness, contraindication for MRI (pacemaker), without ventricular-tachycardia or v-fib, IDDM, cancer and reside within reasonable proximity to OHSU (Oregon and Washington counties close to Portland) and Oregon (counties include Multnomah, Clark, Clackamas, Washington, Columbia, Polk, Marion, Deschutes) and are eligible for recruitment. Assuming 20% of these elders have no evidence of WMH burden and plasma EPA+DHA above 110 ug/mL, 5,256 elders remain potential study participants. To meet our target of 150 subjects enrolled at baseline, we would need to recruit <3% of this population. In addition, the NIA-Layton Aging & Alzheimer's Disease Center maintains direct contact for its ongoing longitudinal aging studies in over 50 aging centers, retirement communities and community organizations in the Portland metro area. Research Data Warehouse at OHSU will identify people with a profile making participation possible. Partnership with the Vancouver Clinic (TVC) has been established for study recruitment. TVC has conducted an EPIC Query and identified ~3,200 patients who match our inclusion criteria. TVC has agreed to release this data to OHSU after sending an opt-out letter to potential participants. Those who do not respond to the opt-out letter in two weeks' time will be contacted by the OHSU research staff.

**Description of study visits (see Study Event Schedule below)**

The MRI, cognitive and other behavioral, functional, and motor measures are collected annually. We will collect blood based biomarkers at month 3 and 6 in the initial year of participation to examine short-term changes during therapy. Blood-based biomarkers are collected every 6 months after the initial year is complete. All study visits where blood draws are performed for screening, safety, and blood-based biomarkers will be fasted. For participants who express extreme anxiety about undergoing an MRI scan, one of the co-investigators licensed to prescribe medication may prescribe a mild anti-anxiety medication to be used for these isolated instances.

**Pre-screening (in clinic or by phone).** Prior to an in-person screening, potential participants are identified by the investigative group through routine clinical contact or through a pre-screening process. Prospective subjects will be non-demented and known to meet as many of the inclusion/exclusion criteria as possible. These subjects will attend a clinic screening with a study partner and bring medications that they are currently taking. If study partner is unable to attend clinic screening, a phone interview will be conducted with the study partner, and consent for this will be obtained over the phone. Study subjects will not be considered study participants until they attend the in-clinic screening and clearly relay their understanding of the study protocol, corroborated verbally and through signed informed consent. **If a participant lives over 100 miles from OHSU, or has significant impairment that makes traveling to OHSU difficult, then we will provide the option for the participant to come to OHSU for a combined visit that consists of both aspects of visits 1 and 2.**

**Screen I (visit 1).** Informed consent will be obtained from both the study subject and the study partner when they arrive at the clinic. Demographics and general medical history will be obtained including psychiatric history, family history and history of allergies. A general physical and neurological exam will be performed including vital measures. To accommodate participants' schedules, the general physical and neurological exam may be performed at Screen II (visit 2) instead. A review of pre-study medications for up to 30 days prior to screening will occur. A non-dementia status will be confirmed using the same diagnostic protocol used in the Oregon Alzheimer's Disease center. The MMSE, CDR, GDS, screening labs, safety labs, and the addition of a plasma PUFA index (EPA + DHA in ug/mL or % <5.5% total fatty acids) will be performed. This information will be used to establish the eligibility as outlined under protocol Inclusion/Exclusion criteria. Screen I/Visit 1 will take approximately 2 hours. **If visits 1 and 2 are combined, the participant will be asked**

**to come in fasted for their appointment, and study staff will wait to randomize the participant pending meeting all inclusion criteria.**

Screen I Fail Procedure: Participants who are ineligible for study will be notified and provided an explanation for their ineligibility. The total number of screen failures and justification will be documented. Plasma PUFA index failures are counted and documented.

**Screen II (visit 2).** MRI will identify subjects with high WMH. MRI screen is performed within 56 days of the Screen I (visit 1). This brain scan determines WMH eligibility as outlined in the protocol Inclusion / Exclusion criteria. This visit will take approximately 3 hours. Participant will also complete a Food Frequency Questionnaire administered by a nutritionist in clinic to answer questions and assure complete data, and central blood pressure will be measured by a research coordinator. The general physical and neurological exam will also be completed if not done at Screen I (visit I).

Screen II Fail Procedure: Participants who are ineligible for study will be notified and provided an explanation for their ineligibility. The total number of screen failures and justification will be documented. WMH volume failures are counted and documented.

**Month 12, 24, 36 (visit 7, 11, 15).** These clinic visits will collect MRI, Behavioral/Cognitive, and Functional measures. Vitals, a physical and neurological exam, safety labs and blood-based biomarker will be completed. Adverse events and concomitant medications will be recorded; study medication will be assessed for compliance and dispensed. At the month 36 visit, the participant will complete the Food Frequency Questionnaire administered by a nutritionist. At month 12 an ECG and RNA will also be collected. These visits will take approximately 5-6 hours. If the participant has a significant impairment that makes coming to OHSU for an extended time too difficult, we will provide them the option to split the visit between two days. The visit will be divided as such that the MRI will take place on a day separate from behavioral/cognitive testing and functional measures. The two visits will occur within 28 days of each other.

| Table 7. Study Event Schedule       |          |           |      |   |   |   |    |    |    |    |    |    |    |    |    |
|-------------------------------------|----------|-----------|------|---|---|---|----|----|----|----|----|----|----|----|----|
| Visit number                        | 1        | 2         | 3    | 4 | 5 | 6 | 7  | 8  | 9  | 10 | 11 | 12 | 13 | 14 | 15 |
| Visit name/Month                    | Screen 1 | Screen II | Base | 3 | 6 | 9 | 12 | 15 | 18 | 21 | 24 | 27 | 30 | 33 | 36 |
| Consent                             | X        |           |      |   |   |   |    |    |    |    |    |    |    |    |    |
| Demographics/Medical history        | X        |           |      |   |   |   |    |    |    |    |    |    |    |    |    |
| Medications                         | X        |           | X    | X | X | X | X  | X  | X  | X  | X  | X  | X  | X  | X  |
| Food Frequency Questionnaire        |          | X         |      |   |   |   |    |    |    |    |    |    |    |    | X  |
| Vitals                              | X        |           | X    | X | X |   | X  |    | X  |    | X  |    | X  |    | X  |
| MMSE                                | X        |           |      |   |   |   | X  |    |    |    | X  |    |    |    | X  |
| Clinical Dementia Rating-SOB        | X        |           |      |   |   |   | X  |    |    |    | X  |    |    |    | X  |
| Geriatric Depression Scale          | X        |           |      |   |   |   | X  |    |    |    | X  |    |    |    | X  |
| Physical and neurological           | X        |           |      |   | X |   | X  |    | X  |    | X  |    | X  |    | X  |
| ECG                                 |          |           | X    |   |   |   | X  |    |    |    |    |    |    |    |    |
| Screening labs          | X        |           |      |   |   |   |    |    |    |    |    |    |    |    |    |
| Safety labs             | X        |           |      |   | X |   | X  |    | X  |    | X  |    |    |    | X  |
| MRI                                 |          | X         |      |   |   |   | X  |    |    |    | X  |    |    |    | X  |
| Neuropsych/Functional Measures      |          |           | X    |   |   |   | X  |    |    |    | X  |    |    |    | X  |
| Blood-based biomarkers  |          |           | X    | X | X |   | X  |    | X  |    | X  |    | X  |    | X  |
| DNA                                 |          |           | X    |   |   |   |    |    |    |    |    |    |    |    |    |
| RNA                                 |          |           | X    | X |   |   | X  |    |    |    |    |    |    |    |    |
| Dispense meds/Randomization         |          |           | X    | X | X | X | X  | X  | X  | X  | X  | X  | X  | X  |    |
| Blinding evaluation                 |          |           |      |   |   |   |    |    |    |    |    |    |    |    | X  |
| Compliance/Pill count               |          |           |      | X | X | X | X  | X  | X  | X  | X  | X  | X  | X  | X  |
| Adverse events                      |          |           |      | X | X | X | X  | X  | X  | X  | X  | X  | X  | X  | X  |

NCI–Food frequency questionnaire; CBC, CMP, TSH, B12, EPA+DHA for entry; CBC, CMP, PT/INR; Fatty acids, endothelial function markers (sICAM-1, sVCAM-1, E-selectin), inflammatory (TNF-alpha, IL-6, hsCRP), amyloid metabolites, lipid fractions

**Blinding and Randomization.** This is a blind placebo controlled study. Based on passing all screening criteria, subjects will be assigned to treatment group using a modified randomized minimization algorithm . The placebo group will be matched to the experimental group in the following factors: age group (5 year categories), sex, education, global CDR scores and WMH volume. The participants, study investigators, research associates, and study coordinators will have no knowledge of study assignment. Data analysis will be performed blinded to treatment status. The project biostatistician ([name]) will create the randomization scheme and will ensure blinding of all study medications and data records. Study medication will be handled, labeled, and distributed by pharmacists in Research Pharmacy Services (RPS) who are independent of the study otherwise. We will also evaluate the effectiveness of our blinding by giving study evaluators, subjects, study partners, and investigators a short questionnaire asking about knowledge of group assignment. The randomization code will be broken only after data analysis or if there is an unusual circumstance, such as numerous serious adverse events before the end of the study.

**Adverse events.** Adverse events will be monitored in “real time” with weekly review of AE’s with study staff using clinical judgment to determine reporting to IRB and FDA. An external data safety monitoring board (DSMB) will convene biannually to study unblinded data on AE coded by organ system. Although assessment of AEs will also include solicitation of non-specific change (e.g., “do you feel different since beginning the treatment?”), a 12-item AE checklist covering all major organ systems will be included to probe for AEs. The nature of each AE, its severity (mild, moderate, or severe), its likely relationship to study treatment (definite, probable, possible, not related, or unknown), its duration, and any necessary treatment modifications or adjustments will be recorded. In addition to the monitoring and recording of AEs at each 3 month subject contact, labs to assess basic metabolic function (including liver function tests), CBC and PT/INR are performed at screening and at months 6, 12, 18, 24 and 36. Incident use of oral anticoagulant therapy is identified through subject interview that occurs every 3 months. Incident anticoagulation therapy cases are asked to stop the supplement and complete complete the remaining follow up visits. Participants will be reminded and encouraged during clinic visits and phone checks to contact the study coordinator or investigator if a moderate or serious AE occurs.

**Compliance:** Compliance will be measured in-clinic by pill count. In addition to the in-clinic checks on compliance, each subject will receive a phone call to check on compliance every 3 months. If a subject’s compliance drops < 80% at any time, they will be contacted by the trial coordinator by phone to find out why

and to aid the subject in finding ways to increase compliance. Although plasma fatty acid measurement is an independent measure of compliance, knowing the results of fatty acids levels during the study would un-blind the study. Plasma PUFA index will be used during data analysis to corroborate pill count.

**Statistical Analysis:** **Aim 1: Determine pufa effects on WMH accumulation over 3 years in non-demented elders, age  $\geq 75$  with low plasma pufa status and WMH burden at entry.** This aim will test the hypothesis that pufas slow WMH accumulation compared to the placebo. **Aim 2: Determine pufa effects on biomarkers of endothelial function.** This aim will test the hypothesis that pufas improve plasma measures of endothelial function. **Aim 3: Determine pufa effects on cognitive change.** This aim tests the hypothesis that pufas slow the executive function and processing speed decline, an effect mediated by WMH.

**Analytic approach.** First we will conduct univariate analyses using changes in WMH progression (**Aim 1**), ICAM-1 (**Aim 2**), and cognitive test scores (**Aim 3**) between baseline and three follow-up assessments (baseline, 12, 24 and 36 month) for WMH, ICAM, and cognitive outcomes with a predictor variable being pufas active vs. placebo. Student's t-test will be used for this descriptive analysis based on ITT. Next we apply linear mixed effects multiple regression models with longitudinal WMH progression (**Aim 1**), sICAM-1 (**Aim 2**), and cognitive test scores (**Aim 3**) as outcomes, a main predictor variable as a dummy variable for pufas (active vs. placebo as a reference) and its interaction with a time variable. Control variables include age at baseline, sex, past history and incidence of vascular diseases including hypertension, ApoE4 allele and depression. Intercept and time variables in years (years from baseline) are treated as random effects in all models. We will use an unstructured error covariance structure and estimate parameters using restricted maximum likelihood procedures. Missing data points in the analytical sample are considered missing at random^69 and the above approach is adequate under this assumption. Interaction term between the pufa and placebo groups and time is of our substantive interest. That is, we are interested in examining the magnitude and significance of the difference in time slopes between the active and placebo groups. In all models quadratic and higher order time variables will be included if it improves the model fitness. The overall fit of the models will be examined using a combination of formal fit criteria and visual inspection of residual plots. Results will be considered significant at  $p < 0.05$ , but we will also provide Bonferroni-adjusted p-values to correct for multiple statistical tests.

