**A3. Emphasis on WMH as a vascular component is of significant interest to dementia prevention strategies.** The prevalence of cerebral WMH in non-demented elders age 65 and older is estimated at 60 - 92%. Cross-sectional studies have shown WMH associated with worse cognitive function, worse scores on tests of activities of daily living and a higher likelihood for dementia. Prospective observational studies have found baseline WMH volume as a strong predictor of the progression of WMH. Our group and others have also observed an increased risk for cognitive decline as WMH progress in non-demented elders. Although the cognitive phenotype associated with WMH progression may eventually pervade several cognitive domains, the literature provides consistent evidence in support of executive dysfunction with impaired information processing and cognitive flexibility as early indicators of underlying WMH accumulation. MRI biomarkers of cerebral WMH are readily available to expedite the testing of therapeutic strategies.

**A4. Evidence for cognitive benefits of pufas are in danger of being disregarded on the basis of clinical trials targeting non-vascular mechanisms.** Observational studies draw attention to an important link between fish intake or plasma omega 3 pufa levels and lower WMH volume. One group examined the prevalence (n=4128) and incidence (n=1124) of silent infarcts and differences in WMH grade by fish consumption in the Cardiovascular Health Study, which included people free of any cerebrovascular disease and age 65 and older. After adjustment for important risk factors, higher fish consumption was associated with less WMH burden (**figure 1A**), but not associated with MRI measures of more whole brain atrophy (sulcal and ventricular grades). In another study, our group utilized nutrient biomarker pattern analysis to circumvent the potential for recall bias when asking older people to recall their diet while simultaneously examining the nutrition most readily assessable by the brain. This cross-sectional analysis examined the association of nutrient biomarker patterns with cognitive function (n=104, mean age 87, 62% women, 10% ApoE4 carriers) and MRI measures of WMH and total cerebral brain volume in a subset (n=42, mean age of 92, range 85-101). All study participants were non-demented.

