**Experimental Design.** The design is based upon the observation that WMH volume and advanced age are strong predictors of WMH progression and cognitive decline in non-demented elders. The single-center, randomized, double-blind, placebo controlled clinical trial will test the efficacy of pufas in slowing WMH progression, improving blood-based biomarkers of endothelial function, and slowing decline in executive function and processing speed. The study population consists of non-demented elders age 75 and older who also meet entry criteria for lower plasma pufa status and higher WMH burden at baseline. The intervention is a 50:50 randomization to an active standardized pufa formulation (fish oil extract) vs. a standardized placebo soybean oil over a 3 year period. The pufa formulation and dosage are based on our pilot study and experience with this formulation showing an excellent safety profile and predictable blood concentration. Total WMH volume will be evaluated at entry and annually to analyze the primary outcome. Serially collected plasma samples will be analyzed at baseline, 3 months, 6 months, and then every 6 months to confirm compliance and examine biological activity of the pufas. Neuropsych test emphasis is placed upon domains known to associate with WMH accumulation and pufas and will be collected at baseline and annually. Clinical Dementia Rating-Sum of Boxes and Activities of Daily Living will also be collected in order to determine if there are any more clinically significant effects of the intervention, although we recognize that cognitive and functional change in this relatively healthy population is very modest in this time frame.

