### Sample size calculations:

**Attenuated rate of total WMH progression (Table 8):** The sample size calculation is based upon the information obtained from Oregon Brain Aging Study. Assuming a 40% reduction in WMH progression over 3 years among the active group, we would have 80% power to detect this difference with a sample size of 50 subjects per arm at  $\alpha = 0.05$  (two-tailed). Given that we may have 50% reduction in WMH progression over this period, we would achieve 80% power to detect this difference with a sample size of 32 subjects per arm at  $\alpha=0.05$  (two tailed). Thus, with a conservative estimate of about 30% attrition over 3 years, we will achieve at least 80% power to detect reasonable effect size (40%) with a sample size of 150 subjects at baseline.

| Table 8. Sample size calculations for mean change in WMH progression over 3 years* |                    |                                                  |                               |                            |                               |
|------------------------------------------------------------------------------------|--------------------|--------------------------------------------------|-------------------------------|----------------------------|-------------------------------|
| Power
0.80                                                                      | Effect
size (%) | Difference in change
between pufa and placebo | Placebo:
Mean (SD) changes | PUFA: Mean (SD)
changes | Sample size
needed per arm |
|                                                                                    | 40                 | 2.8                                              | 7.0 (5.0)                     | 4.2 (5.0)                  | 50                            |
|                                                                                    | 50                 | 3.5                                              | 7.0 (5.0)                     | 3.5 (5.0)                  | 32                            |

\*Derived from Oregon Brain Aging Study cohort data in participants age 80 and older with total WMH volume  $\geq 6$  cm^3

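### The primary slope model omits baseline WMH volume, education and CDR, all minimisation factors, and gives only treatment a time interaction, so its covariates barely adjust the tested contrast and precision is lost

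*Protocol*

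**What the plan says.** Under Blinding and Randomization, the placebo group is to be "matched to the experimental group in the following factors: age group (5 year categories), sex, education, global CDR scores and WMH volume". The description of the baseline visit (visit 3) names the same five factors for the minimisation algorithm.

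Under Statistical Analysis, Analytic approach, the linear mixed model has "a main predictor variable as a dummy variable for pufas (active vs. placebo as a reference) and its interaction with a time variable", with random intercept and random slope in years from baseline. The difference in time slopes between the arms is named as the substantive interest. The control variables listed are baseline age, sex, history and incidence of vascular disease including hypertension, ApoE4 and depression. Baseline WMH volume, education and CDR are not among them, and no covariate is given an interaction with time.

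Section A3 of Significance states: "Prospective observational studies have found baseline WMH volume as a strong predictor of the progression of WMH". The Experimental Design paragraph rests the design on WMH volume and advanced age as strong predictors of WMH progression.

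The sample size section uses the raw SD of the 3-year change (5.0) without covariate adjustment and claims "80% power to detect this difference with a sample size of 50 subjects per arm".

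**The concern.** The protocol enriches on WMH volume, balances allocation on it and calls it a strong predictor of the outcome, then leaves it out of the primary model. Age is in the model, but as written only where it can move the intercept.

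Two things are at stake. The first is precision: baseline values that explain part of the person-to-person variation in progression are collected but not used on the slope. The second is agreement between design and analysis. When allocation balances a prognostic factor and the analysis ignores it, the estimate varies less between hypothetical trials than its model standard error says, so the test is conservative.

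A baseline WMH main effect alone would not help. If the time-0 scan is part of the response and the arms are free to differ at time 0, the slope contrast makes no use of the baseline value.

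**Working it through.** **1. Inputs.** From Sample size calculations and Table 8: mean 3-year change 7.0 on placebo and 4.2 on active, difference 2.8, SD 5.0 in each arm, two-sided alpha 0.05, and "a conservative estimate of about 30% attrition over 3 years". Allocation is 1:1. 150 × 0.70 = 105 completers, about 52 per arm. Not in the protocol, and therefore assumed: the correlation ρ between baseline WMH and 3-year change.

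**2. The plan's own figures.** n per arm = 2(1.960 + 0.842)² × SD² / difference².
- 40% reduction: 2 × 7.849 × 25 / 2.8² = 50.06, against 50 stated.
- 50% reduction: 2 × 7.849 × 25 / 3.5² = 32.04, against 32 stated.

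Both reproduce. At 52 per arm, power is 81.5% by the normal formula and 80.7% by the t-test.

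**3. Why a main effect does not adjust the slope.** With scans at 0, 1, 2 and 3 years for everyone, the treatment-by-time coefficient is the difference between arms in mean within-person slope. A covariate that is constant over time moves a person's whole line up or down and leaves the slope alone. Simulation with random intercepts and slopes (52 per arm, 3-year change SD 5, scan-level residual SD 1.0 assumed, 800 replicates per setting) gave these standard errors per year for treatment by time:

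| Assumed R² of covariate for 3-year change | No covariate | Main effect only | Covariate × time |
|---|---|---|---|
| 0.10 | 0.326 | 0.326 | 0.310 |
| 0.20 | 0.326 | 0.326 | 0.292 |
| 0.30 | 0.326 | 0.326 | 0.273 |

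The estimates in the first two models agreed to about 5 × 10⁻¹⁴. With 75 per arm, about 30% random dropout and R² = 0.20, individual estimates did differ, but precision did not improve: power was 90.1% with no covariate, 89.8% with the main effect and 95.5% with covariate × time.

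**4. Power if baseline WMH acts on the slope.** Residual SD = 5 × √(1 − ρ²), two-sample t-test, 52 per arm, difference 2.8:

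| ρ (assumed) | Residual SD | Power |
|---|---|---|
| 0 | 5.00 | 80.7% |
| 0.2 | 4.90 | 82% |
| 0.3 | 4.77 | 84.3% |
| 0.5 | 4.33 | 90.4% |

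**5. Effect of minimisation.** At 52 per arm the unadjusted model standard error of the 3-year difference is 5 × √(2/52) = 0.98. Simulating allocation minimised on WMH at ρ = 0.5, the true SD of the unadjusted estimate was 0.88. The unadjusted test had type I error of about 3% and power of about 83%, against about 91% adjusted. With near-perfect balance and R² = 0.10, type I error was about 4%, and power 82% unadjusted against 85% adjusted. These runs are illustrative, because the protocol gives neither the WMH categories nor the allocation probability.

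**The case against.** **The covariate list may not be final, and the SAP is not shown.** The protocol does not say how the control variables enter, and a list introduced as including certain variables can be read as open. That is fair as to detail. But the protocol did not defer the model: it names the covariates, the one interaction, the random effects and the estimation method. On its face that specification leaves out three allocation factors and does not adjust the slope.

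**The result for main effects is not universal.** This stands. It is exact only for time-constant covariates with complete data. Incident vascular disease, if coded as time-varying, could move the slope estimate, and the trial expects about 30% attrition.

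**Minimisation already protects against WMH imbalance.** This stands. A reader might infer that chance differences in baseline WMH pass directly into the slope difference. Because WMH volume is a minimisation factor, only residual imbalance remains. Balance also secures part of the precision in advance: at ρ = 0.5 the true SD falls from 0.98 to 0.88 without any adjustment. Much of what adjustment then adds is a standard error that reflects this.

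**The gain rests on an assumed correlation.** This stands too. Entry at WMH of 5 cc or more restricts the range and may weaken the correlation. A reader might take the 28.5% in the summary of preliminary studies as the missing R². It cannot serve, because it relates plasma pufas to WMH volume, not baseline WMH to progression.

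**Education and CDR.** Nothing in the protocol shows that either predicts WMH slope. The case for including them is consistency with the allocation scheme, not a documented gain in power.

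**Conclusion.** The concern holds as a matter of efficiency and of agreement between allocation and analysis. The written model tests a slope difference, gives time-constant covariates essentially no influence on it, and omits baseline WMH despite the protocol's own account of its importance.

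A reader might go further and infer that the trial is underpowered or the test invalid. The document does not support that. The planned 80% power rests on the unadjusted SD and reproduces, and the error in the standard errors is on the conservative side.

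The forgone power is about 1 to 2 percentage points at ρ = 0.2, about 4 at 0.3 and about 10 at 0.5, from a base of 80.7%. These figures assume 52 completers per arm, the Table 8 difference and SD, and a correlation the protocol does not supply. The direction is secure and the size is not. The change should be made, but the trial does not fail without it.

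**What to change.** In the primary WMH model, use one of two forms:
- post-baseline WMH as the response, with baseline WMH and baseline WMH × time as covariates; or
- baseline kept in the response, with the arms constrained to a common mean at time 0.

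Add age × time. Include the remaining minimisation factors (sex, education, CDR) as covariates, with time interactions optional. State explicitly which covariates interact with time. Treat each outcome's own baseline in the same way for ICAM-1 and the cognitive tests.

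Fix this in writing before unblinding. All the values are collected at or before randomisation, so the cost is wording and a few model degrees of freedom out of 150 participants. The sample size need not change.
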